### Training

The 30-h technical training of nurse researchers will be carried out over a one-week period and will be based on a training manual developed for the study, which will include a combination of presentations, participatory activities, readings, reflections, and role-play exercises. The following topics will be covered in the manual and training curriculum: improving knowledge and awareness around intimate partner violence and how it links with maternal and child health issues, and specifically with HIV transmission and adherence to PMTCT; understanding the legal rights of women experiencing violence in the study context; promoting mental health among the study population; awareness of previous and current trauma in the lives of participants; child protection services and reporting obligations within the legal framework; cycle of violence patterns; behaviour change and assessing women’s readiness to change; safety planning; community resources; self-care, relaxation, and dealing with vicarious trauma. Clarifying values and perceptions about violence based on individual or observed experiences is also an important component of the training. A trained clinical psychologist and social workers will be available for counselling and discussion with the nurse researchers in the event they feel the need for emotional support or if they experience an emotional response to the content of the training. The nurse researchers will also be trained on the ethical and safety issues specific to research on violence against women and how to identify and report on adverse events and serious adverse events.

Weekly team meetings will offer a chance to debrief about patient encounters and discuss relevant “case studies”. This process will further familiarize nurses with the components of the intervention and how to implement a second session. Throughout the discussion of “case studies”, the study investigators will provide feedback to the team on how to implement the components of the intervention in a standardized yet tailored manner. Weekly meetings will also be an opportunity to stress the importance of ensuring that participants randomized to the control group are not intentionally or inadvertently given components of the intervention, which is a potential limitation in the study design. Group supervision will be supplemented by a trained social worker affiliated with the study, who can give guidance to nurse researchers on patient care as needed.

### Process evaluation

Process evaluations of clinical trials are important for understanding and interpreting findings from a trial, in particular why an intervention may or may not lead to intended outcomes [42, 43]. A process evaluation will be conducted over the course of the study to evaluate the feasibility and safety of the intervention implementation, the strengths and weaknesses of the intervention content, and the mechanisms through which the intervention impacts outcomes. For this component, a mixed methods approach will be used. Qualitative methods will include in-depth interviews with participants, nurse researchers and health workers in the study clinics; observations of the intervention sessions; structured reflection diaries kept by nurse researchers; and review of meeting reports from team meetings with nurse researchers discussing study implementation. Quantitative methods will include review of safety information from case report forms, review of adverse event and serious adverse event reports, analysis of intervention checklist reporting form completed by nurses for each participant, analysis of safety related questions in the database. The process evaluation will explore the factors that helped or hindered women’s uptake and use of the intervention, factors that helped the nurses provide the intervention effectively, as well as improving understanding about the pathways of change for women who responded to the intervention. The practical considerations of implementing a health sector based intervention will be assessed, and the potential mechanisms of how the intervention impacts change will also be explored.

### Data management

Data collection will be done on paper case report forms (CRFs) and data kept in locked cabinets until they are transferred to the central office and reviewed in a data quality check by the data manager. The data manager will also compare responses in the screening logs with responses in the CRFs to confirm the accuracy of the screening logs. Since patient records are not kept at clinics but rather are carried with them from appointment to appointment, the screening logs and some components of the CRFs will be considered source documents for the trial. Screening logs and CRFs will be scanned and uploaded to a secure location accessible by the Geneva data management team. Data entry will occur at WHO in Geneva. Open Clinica software [44] will be used for data management.

The UNDP-UNFPA-UNICEF-WHO-World Bank Special Programme of Research, Development and Research Training in Human Reproduction (HRP) serves as sponsor for the study. Clinical studies supported by WHO are carried out according to the International Conference on Harmonization (ICH) Good Clinical Practice (GCP) standards, and WHO/HRP standard operating procedures (WHO/HRP SOPs) in the design of the study, data collection, management, analysis, and interpretation of data. HRP standard operating procedures (SOPs) for managing clinical trials will be adhered to throughout the trial. These procedures have been used in previous trials sponsored or coordinated by WHO. The roles and responsibilities of all individuals and institutions involved in the design and conduct of the study, including the study sponsor, study staff, study investigators, steering committee, and the Data Safety and Monitoring Board (DSMB) are clearly described in the SOPs. Data quality will be monitored through 100 % visual checking of CRFs and screening logs at site by data manager and through additional visual checks by the data analyst in Geneva. There will also be query reporting once data are entered into the data management system and through file reviews during regular monitoring visits.

Data will be analysed by study arm using an intention to treat analysis and as detailed in a data analysis plan developed for the study. Statistical data will be analysed using Stata [45] and qualitative data from the process evaluation will be analysed using NVivo [46].

### Ethical and safety considerations

Researching violence against women can potentially result in unintentional risks to participants, researchers, and other health personnel involved in the research. To reduce risks, the study will follow strict ethical and safety guidelines, based on the WHO recommendations in *Putting women first: ethical and safety recommendations for research on domestic violence against women* [47]. These include standard ethical measures on informed consent, confidentiality, and voluntary participation, as well as additional measures related to risks in conducting research on violence against women. For example, nurse researchers are specially trained in inquiring about violence experience sensitively and in a supportive manner. They are expected to carry out all interviews in total privacy and keep all information, in particular intimate partner violence and HIV status of women, confidential. They will also invite women to keep their involvement in the study to themselves, to avoid any safety risk from study participation. Any mention of the study by the study team or clinic nurses will describe the study as a study on women’s health and safety during pregnancy. This type of language prevents stigmatization of women participating in the study. Referral networks have been established so that women can seek additional services from organizations in the community.

All adverse events and serious adverse events reported by participants or by clinic staff to study nurses will be documented and reviewed by study investigators to determine whether the event was unrelated or possibly, probably or highly probably related to IPV and to study participation. All events will be followed up until resolved and medical records will be sought when further information is required. Those events deemed possibly, probably or highly probably related to study participation will be escalated and reported to the Data Safety and Monitoring Board (DSMB). The DSMB will be comprised of a statistician, an epidemiologist and a researcher specializing in gender-based violence and will conduct periodic reviews of the data when 25 %, 50 %, 75 % and 100 % of the blinded follow up data of the target sample is collected. They can request the unblinding of the data and the discontinuation of the study if warranted by the preliminary results. They will review monthly reports of adverse events and serious adverse events and will review all adverse events or serious adverse events assessed by investigators as being”probably” or “highly probably” related to study participation. The DSMB will advise on any protective actions that should be taken.

Ethical clearance was granted by the Human Research Ethics Committee of the University of the Witwatersrand, Johannesburg, South Africa (M110832) and the Ethical Review Committee of the World Health Organization in Geneva, Switzerland (RPC471).

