**Methods:**

Following a formative research phase, a randomized controlled trial will be conducted to test a nurse-led empowerment counselling intervention, originally developed for high-income settings and adapted for urban South Africa. The primary outcome is reduction of partner violence, and secondary outcomes include improvement in women’s mental health, safety and self-efficacy. The study aims to recruit 504 pregnant women from three antenatal clinics in Johannesburg who will be randomized to the nurse-led empowerment arm (two 30-min counselling sessions) or enhanced control condition (a referral list) to determine whether participants in the intervention arm have better outcomes as compared to the those in the control arm.

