The randomized controlled trial (RCT) will test the efficacy of an intervention to address partner violence during pregnancy. Women screening positive for violence and who satisfy the eligibility criteria will be randomized to the intervention or control group (Fig. 1). The intervention group will receive up to two sessions of a counselling intervention and both groups will receive a brief information sheet with local referrals, including for counselling, shelters, legal resources, child protection services, police, and other relevant NGOs. Each of the listed referrals was contacted and its willingness and capacity to respond to referrals during the course of this study was assessed. Selected agencies will be included as active referral options. The protocol complies with the guidelines of the Standard Protocol Items: Recommendations for Interventional Trials (SPIRIT), and all data collection is in compliance with Consolidated Standards of Reporting Trials (CONSORT) guidelines.

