### Recruitment and randomization

Pregnant women will be screened for eligibility. Those who are at least 18 years old and less than 33 weeks gestation (to allow enough time for the second intervention session) and who are able to communicate in one of the most common local languages (English, Sotho, or Zulu) will be eligible to participate in the randomized controlled trial. Potential participants will also be asked if they have experienced any of a number of forms of partner violence in the past 12 months. Only those reporting that they have experienced physical or sexual violence by their current or most recent partner in the past 12 months will be eligible. Prior to being enrolled, women will also be screened for immediate safety risk. Reported risk of imminent lethal violence by a partner, fear that a child in the home is at immediate risk of lethal violence by the partner, and being at suicidal risk (as determined by having ideation with a plan to commit suicide) will result in an immediate referral and disqualify women from participating.

Women will be recruited during their routine antenatal appointments at primary healthcare clinics in urban Johannesburg. All clinics are part of the district public health service and generally serve very low income communities. The study will be introduced by a research nurse, who will provide a group introduction to the study without identifying the study as being related to violence but rather framing it as a study on women’s health during pregnancy. A study flier will be distributed with the name of the study and a phone number and first name of the research nurse assigned to that clinic site. Interested women will be offered an opportunity to speak to nurses following their routine clinic care or to schedule an appointment for another time.

Randomization will be conducted through block randomization procedures with study arm assignment revealed upon opening of sequential opaque sealed envelopes prepared in Geneva by the Department of Reproductive Health and Research, World Health Organization. Study nurses will not be blinded to study arm; the same nurse who conducts the baseline interview will also randomize eligible participants.

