### Follow up

Women will be followed up either at their six weeks’ post-partum visit, when they come for their post-natal check-up or immunization for their baby, by phone or at a time arranged with the study nurse. An estimated 15 % of loss to follow up is expected based on other studies in this setting.

All women who experience an adverse event or serious adverse event will be followed up until it is resolved or she is in stable care. For the purposes of this study, an adverse event will be defined as any untoward medical occurrence or harmful event that affects the health or well-being of a study participant or her infant while participating in the study. A serious adverse event is defined as any untoward medical occurrence or harmful event that results in the death of a participant or her infant, is life-threatening, requires inpatient hospitalization (other than for routine delivery) or prolongation of existing hospitalization, or results in persistent or significant disability.

A recruitment period of 18 months with an additional 6 months of follow-up will be needed to recruit a sufficiently large sample size, assuming exclusions for ineligibility, refusal to participate, and loss to follow up.

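### Adverse events are captured through reports to unblinded nurses, and only the intervention arm has a described extra nurse session before follow-up, so safety ascertainment may be unequal between arms

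*Protocol article*

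**What the plan says.** **Route of capture.** Ethical and safety considerations states that "All adverse events and serious adverse events reported by participants or by clinic staff to study nurses will be documented". Two channels are named, participants and clinic staff, and both lead to the study nurse. Recruitment and randomization says these nurses are not blinded, and that the nurse who does the baseline interview also randomises.

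**Contacts by arm.** The text under Objectives says "The intervention group will receive up to two sessions of a counselling intervention and both groups will receive a brief information sheet with local referrals". The second session is a separate, later encounter: the gestation limit in Recruitment and randomization is set at "less than 33 weeks gestation (to allow enough time for the second intervention session". For control women the article describes the referral list and no interim session.

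**Common follow-up.** The Follow up section makes no distinction by arm. Women are seen about six weeks post-partum, "when they come for their post-natal check-up or immunization for their baby, by phone or at a time arranged with the study nurse". Expected loss is 15%.

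**What counts, and how it is used.** An adverse event is "any untoward medical occurrence or harmful event that affects the health or well-being of a study participant or her infant", with the same definition for everyone. The process evaluation, which is to judge feasibility and safety, includes "review of adverse event and serious adverse event reports" as well as safety-related questions held in the database. The DSMB sees monthly event reports and may ask for unblinding and for discontinuation.

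**The concern.** When harms are recorded as they come to a nurse's attention, the number recorded depends on how often women meet a nurse and what they talk about. The second session deals with danger, escalation and safety strategies (The intervention), so it is an occasion on which harm is likely to be mentioned. No matching occasion is described for control women between baseline and follow-up.

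With equal true rates, the intervention arm could show more events, or show them sooner. Two errors become possible: an unwarranted worry about the counselling, or a real excess put down to reporting. Safety is a live question here, because counselling about a violent partner could itself carry risk. The Discussion lists unblinded nurses and their overlapping roles as limitations, but not unequal capture of harms.

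**Working it through.** The article gives no adverse event rate, count or detection probability, so there is no planned figure to reproduce. The check has two parts.

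**1. Described nurse contacts, side by side**

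| Period | Intervention | Control |
|---|---|---|
| Baseline interview and randomisation | yes | yes |
| Between baseline and follow-up | second session (up to two sessions in all) | none described |
| About six weeks post-partum | yes | yes |
| Clinic-staff report or self-report | open | open |

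The arms differ in the second row only. A woman enrolled just under 33 weeks and delivering at 40 weeks (assumed) reaches follow-up at about 40 + 6 = 46 weeks, so the interval is about 46 − 33 = 13 weeks. It is longer for earlier enrolment.

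**2. Illustration of size**

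From the article: 252 women per arm (Sample size). Assumed, because the article gives none of them:
- p = true event rate, equal in both arms
- f = share of events detected through the routes common to both arms (follow-up, self-report, clinic staff), varied from 50% to 100%
- w = share of events that occur before the second session, 0.25 or 0.50
- s = chance that the second session brings out an event otherwise missed, 0.8, with every intervention woman attending

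Formulas:
- detected, control = 252 × p × f
- detected, intervention = 252 × p × [f + (1 − f) × w × s]
- ratio = [f + (1 − f) × w × s] / f, which does not depend on p

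Worked case, f = 0.5 and w = 0.5: (0.5 + 0.5 × 0.5 × 0.8) / 0.5 = 0.70 / 0.50 = 1.40.

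| f | ratio, w = 0.25 | ratio, w = 0.50 |
|---|---|---|
| 50% | 1.20 | 1.40 |
| 70% | 1.09 | 1.17 |
| 90% | 1.02 | 1.04 |
| 100% | 1.00 | 1.00 |

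At p = 10% there are 25.2 true events per arm. With f = 50% the detected counts are 12.6 in control against 15.1 to 17.6 in intervention. With f = 90% they are 22.7 against 23.2 to 23.7.

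The 1.40 is the top of the values tried, not a bound: smaller f or larger w would raise it. Incomplete attendance at the second session would lower the excess in proportion.

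The table describes final, cumulative counts. In a monthly report many women have not yet reached follow-up. Control events can then have surfaced only through self-report or clinic staff, while intervention events can also have surfaced at the second session. So a timing difference can remain in interim reports even if follow-up eventually captures everything.

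**The case against.** The case against is substantial, and much of it limits the point.

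- **Shared routes exist.** Clinic staff may report in either arm, the study flier carries the research nurse's phone number, and medical records are sought when more information is required. This stands. These routes may be weak for violence, since women carry their own records and are invited to keep their participation private, but they are not nil.
- **No by-arm comparison of adverse events is specified.** Events are assessed one by one for relatedness to violence and to participation, and the general statement that data are analysed by arm does not name them. This stands. The risk attaches to any by-arm reading that the DSMB or the process evaluation makes.
- **The article is condensed.** Fig. 1 was not available in the text reviewed, and the full protocol or SOPs may contain an enquiry common to both arms. This stands as a caveat. If such an enquiry exists, the sponsor need only say so.

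Four stronger readings are tempting and are not supported.

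- A reader might conclude that counts are biased and that control-arm harm is under-detected. The text shows only a risk, which disappears if the shared routes capture all events.
- A reader might attach a fixed excess. Assuming 30% true risk and 60% elicitation per contact gives 0.30 × 0.60 = 18% against 0.30 × (1 − 0.4²) = 25.2%, about 7 points. That requires every event to precede the second session, full attendance, independent elicitation and no other route. If half the events precede the session, the same inputs give 0.30 × (0.60 + 0.40 × 0.5 × 0.60) = 21.6%, or 3.6 points. None of these inputs comes from the article.
- A reader might infer that the 15% lost, 0.15 × 252 ≈ 38 control women, yield no safety information after baseline. They would miss the scheduled follow-up, but self-report and clinic-staff reports stay open. Intervention women who miss the second session and are then lost are in the same position.
- A reader might infer that the primary outcome is contaminated. It is measured separately, with a modified WHO instrument on follow-up data in both arms. The article does not say that new violence is logged as an adverse event, although the wide definition could cover it.

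**Conclusion.** The point holds as a risk of differential ascertainment of harms. Capture runs through reports to unblinded nurses, and one arm has a described extra session with a nurse. The expected direction is more, or earlier, detection in the intervention arm, so the counselling could look less safe than it is.

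The documents cannot fix the size: the ratio is 1.00 if shared routes are complete, and about 1.40 at the least favourable values tried. The conclusion assumes that the article's account of contacts is complete, with no interim contact for control women in Fig. 1 or the full protocol. It concerns the reading of safety data only and leaves the efficacy comparison untouched. It is worth correcting because the correction is cheap.

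**What to change.** 1. At the existing follow-up interview, ask both arms the same structured adverse event questions, in the same words, covering the time since randomisation. If the safety questions already in the database do this, state it.
2. Record the source of every event: second session, follow-up interview, clinic staff or spontaneous report.
3. Keep all events, report all of them to the DSMB, and present them by arm and by source. Use those elicited at the common follow-up as the like-for-like comparison.
4. Exclude no documented event from the overall safety report. Dropping second-session events unless they were elicited again at follow-up would discard genuine events, including serious ones in women who later die or are lost, and would favour the intervention.

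The cost is a source field and a short item set on the follow-up CRF, with no extra visit. The drawback is that the like-for-like comparison depends on recall over several months and covers only women reached at follow-up, which is why the full listing by source must stand beside it.
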